### Blinding

Participants of the RCT will be informed of their intervention condition after all baseline assessments at T0 are completed. The research team will be blind to treatment allocation during the baseline assessments at T0. The team member who runs the R script that allocates participants to one of the treatment groups, will not be blinded to the intervention conditions, but is unaware of therapy conditions when communicating with the participants. The CIDI interviewers will be blind to intervention conditions and will be independent from the therapy coaches. During treatment, therapy coaches will not be blind to the intervention conditions, since they have to provide the participants with feedback on the therapy sessions. During data analyses, all data will be coded regarding intervention condition and analysts will not have access to the key document. Only after statistical analyses are completed, conditions may be revealed.

### Assessment points and measures

In participants of the RCT, repeated assessments take place at baseline (T0), during the 6-week treatment period (T_intervention_), and at four follow-up time points (T1, week 7; T2, week 26; T3, week 39; T4, week 52). Table 1 shows the assessments for each time point (according to the Standard Protocol Items: Recommendations for Interventional Trials (SPIRIT) guidelines; the full SPIRIT Checklist is available as Additional file 1). For all participants, the baseline assessments (T0) include an MRI scan, 9 days of actigraphy monitoring and sleep diaries (Consensus Sleep Diary, CSD [46]), and questionnaires assessing demographics, mood (IDS-SR [43]; Hospital Anxiety and Depression scale, HADS [47]; Positive Affect Negative Affect Scale, PANAS [48]), anxiety (Beck Anxiety Inventory, BAI [49]), sleep (ISI [37]; Pittsburgh Sleep Quality Index, PSQI [50]; Duke Structured Interview for Sleep Disorders for DSM-5, DSISD [51]; sleep history; Munich Chrono Type Questionnaire, MCTQ [52]; reduced Morningness-Eveningness Questionnaire, rMEQ [53]), life events (Life Experience Survey, LES-B [54]), childhood trauma (Childhood Trauma Questionnaire, CTQ [55]), physical exercise (Baecke questionnaire [56]), and cost-effectiveness (Trimbos and iMTA questionnaire on Costs associated with Psychiatric Illness, TIC-P [57]). A diagnostic interview (CIDI-SF [38]) is administered to assess a diagnosis of major depressive disorder according to the DSM-IV criteria [58].

**Table 1 Tab1:** Overview of interventions, assessments, and timepoints

		Study Period					
	Enrolment	Baseline	Intervention	Follow-up assessments			
**Timepoint**	**-t**_1_	**T**_0_	**T**_intervention_	**T**_1_	**T**_2_	**T**_3_	**T**_4_
		*Week 0*	*Week 1–6*	*Week 7*	*Week 26*	*Week 39*	*Week 52*
**Erolment:**							
**Eligibility screen**	X						
**Informed consent**	X						
**Allocation**		X					
**Interventions:**							
***Cognitive Behavioral Therapy for Insomnia (CBT-I)***			X				
***Chronobiological Therapy (CT)***			X				
***Combination of CBT-I & CT***			X				
***Treatment as Usual***			X				
**Assessments:**							
***Demographics***		X					
***CIDI-SF***^1^		X					X
***IDS-SR***^2^		X		X	X	X	X
***HADS***^3^		X		X	X	X	X
***PANAS***^4^		X		X	X	X	X
***Actigraphy***		X		X			X
***CSD***^5^		X	X	X			X
***ISI***^6^	X	X		X	X	X	X
***PSQI***^7^		X					
***DSISD***^8^		X					
***Sleep history***		X					
***MCTQ***^9^		X					
***rMEQ***^10^		X					
***ITQ***^11^	X				X		X
***BAI***^12^		X		X	X	X	X
***LES-B***^13^		X			X	X	X
***CTQ***^14^		X					
***TIC-P***^15^		X					X
***Baecke***		X					
***Compliance***			X				
***Use of interventions***					X	X	X
***Health care use***					X	X	X
***MRI***^16^		X		X			

^1^ Composite International Diagnostic Interview – Short Form, ^2^ Inventory of Depressive Symptoms – Self Report, ^3^ Hospital Anxiety and Depression Scale, ^4^ Positive Affect Negative Affect Scale, ^5^ Consensus Sleep Diary, ^6^ Insomnia Severity Index, ^7^ Pittsburgh Sleep Quality Index, ^8^ Duke Structured Interview for Sleep Disorders, ^9^ Munich Chronotype Questionnaire, ^10^ reduced Morningness-Eveningness Questionnaire, ^11^ Insomnia Type Questionnaire, ^12^ Becks Anxiety Inventory, ^13^ Life Experience Survey, ^14^ Childhood Trauma Questionnaire, ^15^ Trimbos and iMTA questionnaire on Costs associated with Psychiatric Illness, ^16^Magnetic Resonance Imaging

During treatment (T_intervention_), participants randomized to CBT-I (and in combination with CT) fill out the CSD every day during week 1–6 (T_intervention_). Participants randomized to CT (and in combination with CBT-I) fill out a questionnaire about the compliance to the chronobiological interventions every day during week 1–6 (T_intervention_).

The assessments at T1 (week 7) include an MRI scan, 7 days of actigraphy monitoring and sleep diaries (CSD), and questionnaires assessing mood (IDS-SR, HADS, PANAS), anxiety (BAI), and insomnia (ISI). At T2 (week 26) and T3 (week 39) participants fill out questionnaires assessing mood (IDS-SR, HADS, PANAS), anxiety (BAI), insomnia (ISI), insomnia types (ITQ), life events (LES-B), use of therapy interventions and use of health care. After 1 year (T4) participants wear an actigraph for 7 days, fill out sleep diaries for 7 days (CSD), are interviewed to assess a diagnosis of major depressive disorder (CIDI-SF), and fill out questionnaires assessing mood (IDS-SR, HADS, PANAS), anxiety (BAI), insomnia (ISI), insomnia types (ITQ), life-events (LES-B), cost-effectiveness (TIC-P), use of therapy interventions, and use of health care.

### MRI data acquisition

MRI data are acquired using a 3-Tesla MRI scanner with a 32-channel head coil (Philips Achieva, Best, the Netherlands). The following MRI scans are obtained: 1) a T1 weighted image according to the ADNI protocol [59] (repetition time (TR)/ echo time (TE) = 6.5/2.9 ms, voxel size = 1 mm^3^, 211 slices, field of view (FOV) = 256x256x11mm, flip angle = 9°); 2) task-based and 3) resting state functional MRI scans (gradient-echo planar imaging, multi-band factor 4, TR/ TE = 700/30 ms sec, voxel size = 2.7 mm^3^, 44 slices, FOV = 216x216x118mm, flip angle = 55°); 4) Diffusion Weighted Imaging (multi-band factor 2, TR/ TE = 4683/ 95 ms, voxel size = 2 mm^3^, 66 slices, FOV = 224x224x132mm, flip angle = 90°, b = 1000, 29 directions, b = 2000, 59 directions). The task administered during the tasked-based fMRI is from the Human Connectome Project [60] and measures the Blood Oxygen Level Dependent response (BOLD) related to emotional processing. Participants are presented with pictures of emotional faces or neutral shapes. Participants are instructed to indicate which of the two faces or shapes matches the target image. During assessment of resting-state fMRI, participants are looking at a fixation cross for 12 min. Participants are instructed to let their mind wander, think of nothing in particular, and try not to fall asleep. The participant’s eye is video recorded to monitor if participants fall asleep during the scan. The same MRI protocol is used for both the baseline measurement (T0) and the follow-up assessment at week 7 (T1).

### Intervention

Participants will be randomized to one of the following groups: CBT-I, CT, their combination, or treatment as usual.

#### CBT-I

Participants receive guided internet-based, cognitive behavioral therapy (i-Sleep) [15] for 6 weeks. i-Sleep is an internet-delivered CBT-I guided by a personal coach. The i-Sleep treatment module proved to be feasible, acceptable, and effective [15]. i-Sleep consists of 5 weekly sessions to be completed in at most 6 weeks and includes the cognitive and behavioral components that are common for CBT-I. In detail, the five sessions address: 1) Psychoeducation about normal sleep and insomnia, and about sleep hygiene including information about behaviors that are known to stimulate or hamper sleep; 2) stimulus control and sleep restriction: behavioral instructions are given to re-associate the bed/bedroom with sleep and to restrict the time spent in bed to the average amount of night-time sleep; 3) worrying and relaxation: Techniques to reduce worrying and muscle relaxation exercises are proposed; 4) erroneous cognitions about sleep: the basics of cognitive therapy are explained and the most common erroneous ideas about insomnia are addressed; 5) summary and plans for the future. As part of the i-Sleep module, participants complete a sleep diary (CSD) every day.

Each of these sessions contains information, examples, and homework. After finishing each session, the participant receives a personal feedback report by a personal coach, consisting of feedback on participant’s evaluation of previous exercises, their proposed plans, clarifying information and motivating participants to persist in carrying out the requested behavioral changes.

#### CT

Participants receive internet-based CT therapy (i-Cycle) for 6 weeks. i-Cycle is an internet-delivered chronobiological therapy guided by a personal coach. The i-Cycle module is set up in such a way that i-Sleep and i-Cycle can be completed in parallel. Similar to the i-Sleep module, the i-Cycle module consists of 5 weekly sessions that can be completed in at most 6 weeks and includes different components that are commonly considered to support entrainment of the biological clock of the brain. In detail, the five i-Cycle sessions address: 1) Psychoeducation about the circadian rhythm, and about the effect of day and night light exposure on sleep. Participants are taught how to bring structure into their sleep-wake cycle and receive instructions for daily use of the Philips EnergyUp HF3430/01 lamp, shortly after awakening for 30 min at a distance of 40 cm (from eye to lamp); 2) Physical activity: in addition to using the light, participants are informed about the effect of physical activity on sleep and are encouraged to exercise more frequent than usual and/or at a fixed time of day; 3) Physical activity: participants continue the use of scheduled light and exercise while trying to increase the intensity of their physical activity; 4) Temperature: participants receive information indicating that sleep propensity can be enhanced by warming the skin and are instructed to take a warm bath (or a hot shower if no bath is available), for approximately 3 times a week, in the interval 3 to 2 h before bedtime, for 30 min, at a temperature ~ 37–39 °C); 5) Summary and plans for the future. As part of the i-Cycle module a daily activity diary is administered to assess compliance to the interventions.

Each of these sessions contains information, examples, and homework. After finishing each session, the participant receives a personal feedback report by a personal coach, consisting of feedback on participant’s evaluation of previous exercises, their proposed plans, clarifying information and motivating participants to persist in carrying out the requested behavioral changes.

#### Combination of CBT-I and CT

Participants receive both CBT-I and CT as described above.

#### Treatment as usual

Participants do not receive i-Sleep or i-Cycle, but are allowed to seek help from their general practitioner or other specialist (health care use is monitored).

### Outcome measures

The primary outcome is the severity of depressive symptoms during the year following the intervention relative to baseline. Depressive symptoms are repeatedly assessed with the IDS-SR. Mixed effects regression analysis will estimate the integrated treatment effect on all four follow-up IDS-SR assessments from T1 (7 weeks, directly after the six-week intervention) to T4 (52 weeks), relative to T0 (baseline).

### Secondary measures

A secondary outcome is a diagnosis of major depressive disorder based on the CIDI-SF at T4 (52 weeks) relative to T0 (baseline). Other secondary outcome measures are the severity of insomnia and the cost-effectiveness of each treatment calculated from health care and work absenteeism. Severity of insomnia will be measured with the ISI, CSD and actigraphy recordings. Cost-effectiveness will be assessed with the TIC-P questionnaire. Another secondary outcome measure is the effect of the intervention (CBT-I and/or CT) on brain structure and function (assessed with MRI) at T1 relative to T0.

### Sample size calculation

Sample size calculations for mixed effect regression models require a number of estimates, or assumptions [61]. We estimate an average dropout of 3% with every next assessment (all-completers at T0, 3% drop-out at T1 to 12% drop-out at T4). We estimate the (within-subject) intraclass correlation coefficient (ICC) of the pre-assessment and four follow-up assessments to be approximately 0.50. A somewhat higher ICC will slightly inflate the minimal detectable effects, a somewhat lower ICC will slightly lower the minimal detectable effects. In the two by two factorial intervention design, the ratio of participants who will receive CBT-I versus those who will not is 1. This is also the case for those who will receive CT versus those who will not. For the interaction effect of CBT-I x CT, the ratio of participants who will receive both interventions versus those who will not is 1/3. We follow Cohen’s suggestion that an effect size below *d* = 0.2 (small) is not likely to be clinically significant, that *d* = 0.5 represents a medium effect size, and that *d* = 0.8 represents a large effect size [62]. A feasible total number of completers (i.e. complete data on the ambulatory recordings, EEG sleep recordings, MRI and questionnaires) at baseline is *N* = 120, *N* = 30 for each of the four groups, of whom we assume that *N* = 26 per group will complete all follow-up assessments. At a significance threshold of *α*  = 0.05, this sample size provides a power 1-*β*  = 0.80, the minimal detectable interaction effect is *d* = 0.5, while the minimal detectable main effects of either CBT-I or CT are *d* = 0.44 (medium). A previous similar study reported a more than medium effect of CBT-I on depressive symptoms at T1 (*d* = 0.74) up to a large effect at T4 (*d* = 1.12) [63].

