### Statistical analyses

Statistical analyses aim at determining the relative efficacy of internet-guided CBT-I, CT treatments and their combination, for the prevention of worsening of depressive symptoms in people with the type of ID that heralds increased risk of developing depression. The long-term effects of interventions and their interactions on depressive symptoms and on the probability to develop a diagnosis of depression will be estimated with mixed effect linear and logistic regression models using R [45].

In order to allow for an intention-to-treat analysis including all available data while accounting for a possibly variable number of missing data, hierarchical mixed effect linear and logistic regression models will be employed. Regressors are a random intercept, time, dummy-coded assignment to CBT (yes = 1, no = 0) and CT (yes = 1, no = 0) and a dummy coded variable indicating follow-up (T1-T4 = 1) versus baseline (T0 = 0). The interaction effect estimates of interest are CBT by follow-up, CT by follow-up and CBT-I by CT by follow-up [64]. The time variable estimates linear changes over time. Ancillary analyses will evaluate treatment by time effects (i.e., treatment effects changing linearly over time). Linear mixed effect models will also be used evaluate secondary outcomes (insomnia severity, cost-effectiveness, brain function and structure). A logistic mixed effect model will be used to evaluate the secondary outcome of a diagnosis of depression at T4. We will explore the effect of various variables, including the number of previous depressive episodes, time since last depressive episode, and expectation of intervention effectiveness.

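### The stated detectable CBT-I x CT interaction (d = 0.5) belongs to the combination arm against the other three arms pooled; for the interaction in the planned model it is about 0.87

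*Protocol article*

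**What the plan says.** The section Sample size calculation treats each effect as a comparison of two groups with a given size ratio. For a main effect, "the ratio of participants who will receive CBT-I versus those who will not is 1", and the same is said for CT. For the interaction, "For the interaction effect of CBT-I x CT, the ratio of participants who will receive both interventions versus those who will not is 1/3". At alpha 0.05 and power 0.80, with 30 per arm at baseline and 26 per arm completing all follow-ups, the section gives a detectable main effect of d = 0.44 and says that "the minimal detectable interaction effect is *d* = 0.5".

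The section Statistical analyses describes a mixed model with 0/1 indicators for CBT-I, for CT and for follow-up versus baseline. It lists its targets: "The interaction effect estimates of interest are CBT by follow-up, CT by follow-up and CBT-I by CT by follow-up".

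**The concern.** The quantity that was sized and the quantity that will be tested are different.

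- **Sized:** combination minus the average of CBT-I, CT and treatment as usual.
- **Tested:** (combination - CT) - (CBT-I - treatment as usual), each term being a change from baseline to follow-up. With 0/1 indicators and both main effects in the model, this is what the CBT-I by CT by follow-up coefficient estimates.

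The first contrast does not isolate interaction. Suppose CBT-I and CT each had an effect of 0.44 and simply added. The combination would then exceed the average of the other three arms by 0.88 - (0.44 + 0.44 + 0)/3 = 0.59. That is larger than the stated detectable 0.5, although the interaction is zero.

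The combination is part of the primary objective, and the interaction is one of three named estimates on the primary outcome. If the stated power is taken at face value, a non-significant interaction could be read as excluding medium-sized synergy or antagonism, which the design has well under an even chance of detecting.

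**Working it through.** **Inputs, all from the protocol article**

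- Alpha 0.05, power 0.80, 26 completers per arm (Sample size calculation). Sidedness is not stated; two-sided is assumed, so the multiplier is 1.960 + 0.842 = 2.80.
- "intraclass correlation coefficient (ICC) of the pre-assessment and four follow-up assessments to be approximately 0.50" (Sample size calculation).
- Four follow-ups, T1 to T4, analysed together relative to baseline (Outcome measures).

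**Variance factor f, in units of SD²**

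- Mean of four follow-ups: (1 + 3 × 0.50)/4 = 0.625.
- Mean of four follow-ups minus baseline: (1 - 0.50)(1 + 1/4) = 0.625.

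The two agree at ICC 0.50, so the results below do not depend on which was used.

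**Step 1: reproduce the stated figures.** Minimal detectable effect = 2.80 × √[f(1/n1 + 1/n2)].

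- Main effect, 52 versus 52: 2.80 × √(0.625 × 2/52) = 0.434 (0.439 with the t distribution). Stated: 0.44.
- Combination versus the rest, 26 versus 78: 2.80 × √[0.625 × (1/26 + 1/78)] = 0.502 (0.506 with t). Stated: 0.5.

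Both are recovered. A one-sided test would give 0.386 and 0.445, which match neither.

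**Step 2: the interaction in the planned model.** Four arm means enter with weights of +1 or -1, so the variance is f × 4/26.

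- SE = √(0.625 × 4/26) = 0.310.
- Minimal detectable effect = 2.80 × 0.310 = 0.87 (0.877 with t).
- Power at d = 0.5 = Φ(0.5/0.310 - 1.96) = 36%.

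**Step 3: checks that do not need the formula**

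- In a balanced 2 × 2 design the difference of differences has twice the standard error of a marginal main effect. Doubling the protocol's own 0.44 gives 0.88.
- The penalty for a 1:3 split at the same total is √(4/3), and 0.44 × √(4/3) = 0.51, in line with the stated 0.5.
- If the interaction were defined as half the difference of differences, its detectable effect would equal the main-effect figure, 0.43 to 0.44. So 0.5 is not an interaction figure on either scale.

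**Step 4: sensitivity**

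| Setting | Detectable interaction | Power at d = 0.5 |
|---|---|---|
| 26 per arm, ICC 0.50 | 0.87 | 36% |
| 30 per arm with stepwise 3% dropout, planned model, ICC 0.50 | 0.82 | 40% |
| 30 per arm, no dropout, ICC 0.50 | 0.81 | 41% |
| Planned model with dropout, ICC 0.4 | 0.90 | not computed |
| Planned model with dropout, ICC 0.6 | 0.74 | not computed |
| Baseline-adjusted analysis (not the stated model) | 0.63 to 0.67 | not computed |

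The last row would also give a main effect of about 0.31 to 0.34, which does not match the stated 0.44.

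**The case against.** **The ratio describes the product term.** One could say that 1/3 is just the split of the CBT-I × CT indicator, which equals 1 for a quarter of participants. This does not rescue the figure. With both main-effect indicators in the model, the variance of that term is three times that of the simple split, and 0.502 × √3 = 0.87.

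**The figure 0.87 is too firm.** This stands in part. The analysis will use all available data, which gives about 0.82. The ICC is given only as approximate, and the cited sample size method is not at hand. The two variance formulas also move in opposite directions as the ICC changes: the article's remark that a higher ICC inflates detectable effects fits the follow-up-mean formula, whereas the planned model fits the change-from-baseline formula. None of this brings the interaction down to 0.5.

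**The main-effect figure raises its own question.** This also stands, as an adjacent point. The value 0.44 refers to the marginal effect (52 versus 52). With 0/1 coding and the three-way term included, the CBT by follow-up coefficient compares CBT-I alone with treatment as usual, with a detectable effect of 2.80 × √(0.625 × 2/26) = 0.61. The corrected text should say which contrast 0.44 describes.

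**The practical harm is limited.** The article presents 120 participants as a feasible number and does not derive it from the interaction. It nowhere commits to a particular reading of a null interaction. Both are fair, but the stated power remains wrong for a named effect on the primary outcome.

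**Conclusion.** The concern holds. The stated 0.5 is the detectable effect for the combination arm against the other three arms pooled. For the CBT-I by CT by follow-up coefficient it is about 0.87 with 26 completers per arm, or about 0.82 with all available data. Power at d = 0.5 is about 36% to 41%, not 80%. On the Cohen scale that the article uses, the detectable interaction is large (above 0.8), not medium, and falls within the range of the whole CBT-I effect it cites (0.74 to 1.12).

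The exact values assume a two-sided 0.05 test, ICC 0.50, four follow-ups and equal arms. The factor of two between the interaction and the marginal main effect depends only on the balanced 2 × 2 layout. The marginal main-effect figure of 0.44 is reproduced and is not disputed.

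**What to change.** In Sample size calculation:

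1. Delete the sentence giving the 1/3 ratio for the interaction.
2. Replace the interaction figure with a statement that the detectable CBT-I by CT by follow-up effect, expressed as a difference of differences, is about d = 0.87 at 80% power with 26 completers per arm (about 0.82 using all available data), and that power at d = 0.5 is about 36% (about 40%).
3. State that 0.44 is for the marginal effect of each treatment, averaged over the other.

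In Statistical analyses, add that the interaction will be reported with its confidence interval and that a non-significant result will not be taken as evidence of no interaction. Labelling the test exploratory would be sensible but is optional; the correction does not depend on it.

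The cost is wording only. One published figure becomes less favourable. Recruitment, randomisation, data collection and the fitted model are unchanged.

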### Statistical analyses

Statistical analyses aim at determining the relative efficacy of internet-guided CBT-I, CT treatments and their combination, for the prevention of worsening of depressive symptoms in people with the type of ID that heralds increased risk of developing depression. The long-term effects of interventions and their interactions on depressive symptoms and on the probability to develop a diagnosis of depression will be estimated with mixed effect linear and logistic regression models using R [45].

In order to allow for an intention-to-treat analysis including all available data while accounting for a possibly variable number of missing data, hierarchical mixed effect linear and logistic regression models will be employed. Regressors are a random intercept, time, dummy-coded assignment to CBT (yes = 1, no = 0) and CT (yes = 1, no = 0) and a dummy coded variable indicating follow-up (T1-T4 = 1) versus baseline (T0 = 0). The interaction effect estimates of interest are CBT by follow-up, CT by follow-up and CBT-I by CT by follow-up [64]. The time variable estimates linear changes over time. Ancillary analyses will evaluate treatment by time effects (i.e., treatment effects changing linearly over time). Linear mixed effect models will also be used evaluate secondary outcomes (insomnia severity, cost-effectiveness, brain function and structure). A logistic mixed effect model will be used to evaluate the secondary outcome of a diagnosis of depression at T4. We will explore the effect of various variables, including the number of previous depressive episodes, time since last depressive episode, and expectation of intervention effectiveness.

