### Participants

The RCT aims to include 120 people with ID of the subtypes with increased risk of developing depression. Inclusion criteria are: 1) meeting the criteria of ID according to the Diagnostic and Statistical Manual of Mental Disorders, 5th edition (DMS-5) [35], and the International Classification of Sleep Disorders, 3rd edition (ICSD-3) [36]; 2) an Insomnia Severity Index score (ISI) ≥ 10 [37]; 3) classification as insomnia type 1, 2, or 3 according to the Insomnia Type Questionnaire [8]; and 4) age between 18 and 70 years. Exclusion criteria are: a) current major depressive disorder according to self-report, a clinical diagnosis, or the Composite International Diagnostic Interview Short Form (CIDI-SF) [38]; b) current treatment with antidepressant medication; c) current CBT-I treatment; d) a diagnosis of or probable severe obstructive sleep apnea syndrome (Apnea Hypopnea Index ≥15 [39], or high risk according to the Berlin questionnaire [40]), moderate to severe restless legs syndrome (International Restless Legs Scale > 15 [41]), or severe periodic limb movement disorder (Periodic Limb Movement Index ≥ 25); e) a self-reported diagnosis of a severe neurological or psychiatric disorder; f) self-reported severe physical or mental impairment due to stroke, or traumatic head injury; g) night work or rotating shift-work; h) a known eye condition incompatible with light exposure; i) a history of light-induced migraine or epilepsy, or severe side effects to bright light in the past; or j) MRI contraindications such as non-MR compatible metal implants, claustrophobia, or pregnancy. The use of sleep medication is allowed and monitored. Participants will be recruited among the participants of the Netherlands Sleep Registry (www.sleepregistry.org), through media advertisements, and through flyers. It will be documented whether participants were recruited from the sleep registry or via media advertisements and flyers.

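### The statement that the mixed models account for missing data does not hold for MDD at T4: the 14 to 16 of 120 participants expected to be lost carry no information on its treatment effect

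*Protocol article*

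**What the plan says.** The Statistical analyses section gives the reason for choosing mixed models, of both the linear and the logistic type: "In order to allow for an intention-to-treat analysis including all available data while accounting for a possibly variable number of missing data, hierarchical mixed effect". The same section applies this to MDD: "A logistic mixed effect model will be used to evaluate the secondary outcome of a diagnosis of depression at T4". Secondary measures defines the outcome: "A secondary outcome is a diagnosis of major depressive disorder based on the CIDI-SF at T4 (52 weeks) relative to T0 (baseline").

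The schedule comes from Assessment points and measures. Table 1 marks the CIDI-SF at T0 and T4 only, and the text places the follow-up interview at one year, when participants "are interviewed to assess a diagnosis of major depressive disorder (CIDI-SF"). The IDS-SR and HADS are scheduled at T0 and at T1, T2, T3 and T4. Among the exclusions under Participants is "current major depressive disorder according to self-report, a clinical diagnosis, or the Composite International Diagnostic Interview Short Form (CIDI-SF").

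On losses, Sample size calculation assumes "3% drop-out at T1 to 12% drop-out at T4" and takes it that 26 participants "per group will complete all follow-up assessments".

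**The concern.** A mixed model helps with missing outcomes by using a participant's other informative measurements of the same outcome. Someone who leaves after T2 still contributes two follow-up IDS-SR scores, so the rationale is sound for the primary outcome. For MDD there is one follow-up measurement, and the baseline value is the same for everyone. Once T4 is lost, nothing informative is left for the model to use. It also cannot use the IDS-SR or HADS scores from T1 to T3, because they are not in the MDD model.

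The protocol therefore credits this analysis with a property that it lacks. MDD is the first secondary outcome listed and the one closest to the aim of preventing a depressive episode. If leaving the study depends on depressive symptoms, and does so differently in treated and untreated participants, the estimated effect on MDD is biased while the text says that missing data are accounted for.

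**Working it through.** **Inputs.** From the protocol: 120 randomised, 30 per group (Participants; Randomization); drop-out of 3% at T1 rising to 12% at T4, and 26 completers per group (Sample size calculation); ICC 0.50 and minimal detectable main effect d = 0.44 (same section); 13% one-year depression rate in insomnia (Background); CIDI-SF at T0 and T4 (Table 1).

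**1. The plan's completer figure.** 30 × (1 − 0.12) = 26.4, stated as 26. The figure reproduces.

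**2. Missing T4 diagnoses.** 0.12 × 120 = 14.4, about 14. By the rounded 26 per group, 120 − 4 × 26 = 16, or 13.3%. This assumes that those lost at T4 also miss the CIDI-SF interview.

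**3. What a lost participant adds to the logistic mixed model.** With baseline log-odds b0 and random intercept u, a T0 row with no MDD contributes 1/(1 + exp(b0 + u)). As every T0 value is 0, the likelihood rises as b0 falls without limit, and each T0 row then contributes a factor of 1. A participant with a T0 row only therefore contributes 1, whatever the treatment effects are.

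A numerical check used an illustrative 120-person data set: 6, 4, 4 and 3 cases, and 4, 3, 4 and 3 people without T4, in treatment as usual, CBT-I, CT and the combination. Three fits were compared: all 120, T4 completers only, and T4 rows only. In the limit all three gave the same negative log-likelihood (45.9522) and the same coefficients. With random-intercept SD 0 these follow by hand from completers alone:
- CBT-I: ln(4/23) − ln(6/20) = −0.545
- CT: ln(4/22) − ln(6/20) = −0.501
- Interaction: ln(3/24) − ln(4/23) − ln(4/22) + ln(6/20) = 0.171

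The three fits also agreed with each other at random-intercept SD 1 and 2.

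**4. Scale against events.** Expected cases: 0.13 × 120 = 15.6, against 14.4 to 16 missing. Per factor level of 60: 0.13 × 60 = 7.8 cases and 0.12 × 60 = 7.2 missing. If 13% of the 52.8 observed are cases (6.86), the rate in that level is:
- all missing counted as non-cases: 6.86/60 = 11.4%
- all missing counted as cases: (6.86 + 7.2)/60 = 23.4%

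**5. Possible bias (simulation, 1,000,000 per group).** Assumptions not in the protocol: a latent MDD score correlated 0.85 with T4 IDS-SR; a treatment effect equal to the plan's d = 0.44, giving true rates of 13.0% and 6.7%; 12% drop-out in both groups, following the mean T1–T3 IDS-SR in one group only. The true risk difference is about 6.3 points.

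| Log-odds of drop-out per SD | Bias, untreated only (points) | Bias, treated only (points) |
|---|---|---|
| 0.5 | −0.7 | +0.5 |
| 1 | −1.4 | +0.9 |
| 2 | −2.3 | +1.5 |

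With the same mechanism in both groups, the log odds ratio moves only from 0.73 to 0.74–0.76 at slopes 0.5 to 1.

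**6. Does imputation help under the plan's own drop-out pattern?** A loss of 3% at each of four assessments is 0.03 × 120 = 3.6 people per step. Of 14.4 drop-outs, 3.6 (25%) have no follow-up IDS-SR, 3.6 have T1 only, 3.6 have T1–T2 and 3.6 have T1–T3. With staggered losses driven by the last observed score (slope 1), the observed-case risk difference was 5.0 (untreated only) or 7.2 (treated only) points, against a true 6.3–6.4. Multiple imputation gave 6.2–6.4.

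**The case against.** The strongest reply is that a journal article may leave the handling of a missing secondary outcome to the statistical analysis plan. That stands for silence: the absence of an imputation model would be no finding. But this text is not silent. It names a method for this outcome and gives its ability to account for missing data as the reason for choosing it.

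A second reply is that the sentence promises only that available data are used and that participants are analysed as allocated, both of which are true. This stands in part. A reader might infer that the MDD analysis is not intention-to-treat at all. The protocol does not support that: everyone observed is analysed in the assigned group, and an observed-case analysis is valid if missingness depends only on allocation and modelled covariates. What fails is the part about accounting for missing data.

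A third reply is that bias is not shown. This also stands. Nothing in the protocol suggests that drop-out differs by arm, the size depends on an unknown slope, and the biases in the table are small beside the sampling SD of the risk difference in a trial of this size (about 5.5 points).

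Finally, one may say that the real problem is the random intercept, which these data cannot identify. That is a related but separate matter: an ordinary logistic regression at T4 would lose the same participants.

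**Conclusion.** The point holds as a misstatement about one secondary outcome. For MDD at T4 the mixed logistic model does not account for missing data; it amounts to an observed-case analysis, by allocated group, of about 104 to 106 of 120 participants. The 14 to 16 missing diagnoses are about as many as the expected cases, if the cited 13% rate applies.

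A reader might go further and conclude that the MDD effect will be biased, or attach a fixed percentage to the bias. The protocol does not support either. Bias of roughly 0.5 to 2 points on a risk difference of about 6 arises only if drop-out is symptom-related and differs between arms, and the figures rest on the assumed slopes, d = 0.44 and correlation of 0.85. If the mechanism is the same in both arms, the distortion is small. Nor do the scheduled scores fully repair the gap, as about a quarter of those lost would have baseline scores only. The primary IDS-SR analysis is not affected.

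**What to change.** In Statistical analyses, limit the missing-data statement to outcomes measured repeatedly after baseline. For MDD at T4:
- multiply impute missing diagnoses from CBT-I and CT allocation, baseline IDS-SR and HADS, and whatever T1–T3 IDS-SR and HADS scores each participant has;
- analyse all 120 as randomised;
- report the observed-case analysis and best/worst-case bounds as sensitivity analyses.

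No new data are needed. The cost is a change of wording, a little more analysis work and slightly larger variance. In a simulation with 60 per side, the SD of the risk difference was 5.7–5.8 points with imputation against 5.5 without. That run gave every drop-out T1–T3 scores, so it does not show the cost under the plan's staggered losses. The imputed result also relies on missingness being explained by the observed scores, which is why the bounds should be shown beside it.
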